# The comparison between the effects of pain education interventions with online and face-to-face exercise and the control group received biomedical education + standardized physical therapy in patients with chronic nonspecific neck pain during COVID-19: protocol for a parallel-group randomized controlled trial

**DOI:** 10.1186/s13063-022-06932-3

**Published:** 2022-12-20

**Keywords:** PNE, Nonspecific neck pain, Psychological factors, Pain, Disability, Function

## Abstract

**Background:**

Various psychological issues and serious health concerns during the imposed lockdown by coronavirus disease 2019 (COVID-19) have induced many changes in the treatment of patients. More effective self-management strategies through tele-rehabilitation are suggested to be applied for patients with chronic neck pain to reduce referrals to health cares and disability support through COVID-19. Also, the pain neuroscience education (PNE) approach is an educational method used by health professionals to assist patients in understanding the biology, physiology, and psychosocial factors affecting their pain experience and aligning with the cognitions and beliefs associated with pain and recurrent disability. PNE combined with tele-rehabilitation could be a new solution to encourage patients to manage their condition by themselves and increase the continuity of practice instead of face-to-face sessions.

**Objective:**

This randomized control trial (RCT) aims to investigate the effects of PNE with online and face-to-face exercise interventions, and the control group received biomedical education + standardized physical therapy on neck pain and disability, psychological factors, and function in non-traumatic chronic neck pain.

**Methods/design:**

Patients with non-traumatic chronic neck pain (patient-centered care and active involvement of patients and the public) will be recruited via flyers displayed in hospitals and universities to participate in an RCT with two experimental and one control group designed to investigate the effects of PNE with online and face-to-face exercise interventions, and the control group received biomedical education + standardized physical therapy on neck pain and disability, psychological factors, and function in non-traumatic chronic neck pain. The outcomes will be measured at baseline, after PNE, and after 3 months of an exercise intervention. All outcomes are presented as mean ± SD, and statistical significance was set at *α* level of < 0.05. The normal distribution of the variables was verified by the Kolmogorov-Smirnov test, following a descriptive analysis.

**Discussion:**

It seems that PNE plus online and face-to-face exercise interventions are appropriate educational models for the treatment of patients with neck pain during COVID-19. Also, online training seems to encourage patients to continue their treatment.

**Trial registration:**

Iranian Registry of Clinical Trials IRCT20150503022068N5. Registered on 09 September 2021

## Introduction

In 70% of patients with neck pain, there is no defined diagnosis based on the structure involved and mostly no specific cause for neck pain known as nonspecific neck pain [1]. Neck pain mainly affects adults and is associated with decreased quality of life, physical activity, and mental health [2]. Neck pain can be considered a social issue with a significant negative impact on the condition of patients, family, workplace, and the national healthcare system [3, 4].

Chronic pain is defined by the International Association for the Study of Pain (IASP) as pain beyond the normal tissue healing time (more than 12 weeks) [5]. For chronic neck pain, no underlying structural pathology is often found, and radiographic imaging findings are more age-related than patient symptoms [6]. Chronic neck pain is also described as hypersensitivity to the skin, ligaments, and muscles to the touch and passive and active neck and shoulder movements [6]. In 1983, Clifford Wolff stated that chronic pain is not only due to environmental sensitivities but “partly due to changes in spinal cord function.” [7, 8] Psychological factors (such as fear avoidance beliefs and self-efficacy) are involved in the maintenance of pain and transfer from acute to chronic pain [9].

Also, due to the coronavirus disease 2019 (COVID-19), a sudden lockdown of almost all services and activities has resulted in unexpected changes in the lifestyle of people [10] and has severely impaired their psychosocial factors, including increased anxiety, stress, and depression [11]. It has been shown that remote exercise-based treatment in Parkinson’s disease and overweight and obese individuals during the lockdown induced by COVID-19 helped patients overcome psychological issues and fitness concerns [11, 12].

Meanwhile, exercise interventions that encourage self-management are recommended for people with chronic musculoskeletal pain [13–15] and are the basic training of this approach. Due to the bio-psycho-social nature of chronic musculoskeletal pain, it seems that the educational approach based on the bio-psycho-social model is an appropriate educational model for treating these people [16, 17].

Cayrol et al. suggested that pain should be evaluated based on the factors impacting pain or daily activities [18]. Physicians may focus on behaviors such as fear of movement, passive coping strategies, and muscle activity or movement patterns that cause pain [18].

Social and psychological factors and patient preferences are important when initiating treatment planning and building therapeutic alliances [17]. During the initial evaluation, a strong therapeutic alliance can be established by introducing the concepts of pain neuroscience education (PNE) and carefully choosing words to reduce the fear of persistent pain [19]. Also, expressing problems in the patient’s own words provides more accurate information than ready-made checklists [16].

PNE gives comprehensive and adequate information on the nervous system’s response to harmful or potentially harmful stimuli; hypersensitivity to afferent neurotransmitters, such as swelling after acute injury; increased pain response in the central nervous system, hypersensitivity, or increased pain response; and neural plasticity, changes in the nervous system resulting from physical and cognitive activity [16, 19, 20].

Studies have addressed the positive effect of PNE combined with motor control training or neck/shoulder exercises on reducing the present pain, physical function, depression, anxiety, stress, quality of life, and fear avoidance in patients with musculoskeletal pain [21, 22]. However, there is evidence that shows the difference between the groups was only related to pain knowledge in the group using PNE, which could possibly lead to better coping for patients with pain in the future [23]. Louw et al. showed that no training or metaphorical method was recognized as the best to help the recovery process through the use of PNE [24].

Review studies have reported the positive effect of educational strategy based on pain neurophysiology and neurobiology on pain, disability, pain catastrophizing, and physical function [20, 25, 26].

PNE should not be used as a separate treatment method but should be combined with other treatment strategies to increase their effect (synergy) [20, 27]. This has already been investigated in a small study with positive results [28, 29] but should be considered for aggregation in further research with a large sample size and sufficient strength. Future studies should compare the effects of PNE and online exercise with PNE and face-to-face exercise and consider its cost-effectiveness [27].

Online rehabilitation reduces the treatment cost and provides 24/7 online support for home exercises [30]. Supporting exercise at home is important because self-management consistency in exercise is a common problem in exercise therapy [31, 32]. Research shows the importance of continuity of exercise at home, because it has positive effects on pain and physical function [32] and cost reduction [30].

To our knowledge, no randomized control trial (RCT) has examined the differences in the effect of PNE with online and face-to-face exercise interventions in people with chronic neck pain. Therefore, the present study aims to investigate the differences between the effect of PNE with online and face-to-face exercise interventions on neck pain and disability, psychological factors, and function in non-traumatic chronic neck pain during COVID-19. We hypothesized that PNE with online exercise intervention could be more effective than PNE with face-to-face exercise intervention on neck pain and disability, psychological factors, and function in non-traumatic chronic neck pain during COVID-19.

## Methods and study design for RCT

### Sequence generation

This study is a randomized assessor-blind controlled trial. Patients (patient-centered care and active involvement of patients and the public) with chronic non-traumatic neck pain will be recruited via flyers displayed at universities, university hospitals, and primary cares over 3 months in August, October, and November 2021in Mazandaran province, Iran. Patients interested in the study will be asked to email the researchers. All demographic data and inclusion and exclusion criteria will be gathered through online questionnaires, which will be sent in reply to patients. A physician will examine all patients meeting the criteria to ensure the selection process is carried out following the inclusion and exclusion criteria.

If the patient is interested in participating in the study, after signing the informed consent control by the researchers, the baseline data will be gathered by a blind evaluator. The patient will be informed that they can leave the study at any time. Patients in each group will be excluded from the study if they have severe pain (above 8, according to NPRS-11) or did not attend three sessions. After the initial evaluation, patients will be randomly assigned to one of the three study groups (experimental or control) (Fig. 1).

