### Study participants and eligibility criteria

The patients with chronic non-traumatic neck pain who meet the following criteria will be accepted as participants in the trial: patients with chronic nonspecific and non-traumatic neck pain of at least 3 months, visual analog scale (VAS) greater than 3 from 10, both sexes range from 18 to 65, accept to take part in the research, and sign the information concept [27].

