### Randomization

Patients can discontinue the project at any time because of participant request or improving/worsening disease. However, all efforts will be made to avoid missing data. Before starting statistical analyses, the specific way to deal with missing data will be determined at a data review meeting.

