### Primary outcome measurements

The primary outcome will be measured as between- and within-group differences in the Numerical Pain Rating Scale (NPRS) at the second and third assessments.

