#### Numerical Pain Rating Scale (NPRS)

The scale is 11 points for pain reporting. This is the most common pain reporting scale. The patient will choose a number according to the rule (0–10) that best indicates the severity of his pain. The number zero indicates no pain and 10 indicates the most severe or worst pain. (There are different types of numbers from 0 to 10 that one can choose). The scales are categorized as follows: painless (0), mild pain (1–3), moderate pain (4–6), and severe pain (7–10), but these categories do not necessarily reflect the patient’s meanings and for any assessments are poor. These categories may be used to set goals for the outcome of the intervention. NPRS can be done orally (by phone) or graphically. The validity of the NPRS has been shown in patients with rheumatism and other chronic pain conditions (pain > 6 months), ICC has been reported to be 0.95–0.86.40. The MDC reported from the 11-point NPRS is 0.45 [39].

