### Statistical analysis

The study was designed to identify a 2-point difference in pain intensity (30%) assessed by the NPRS across groups, with an expected standard deviation of 2.5 points [55]. For the global perceived effect, there is a difference of 2 points on the scale, with 11 points ranging from − 5 to + 5 [39]. The other specifications were an alpha of 5% and a power of 80%, with a total of 288 patients. However, assuming a 20% drop in follow-up, we will enroll 360 individuals (88 patients per group). G*Power was used to calculate the sample size (GPower 3.0.10, University of Kiel, Germany). The intention-to-treat protocol was followed for post-treatment analysis. See the CONSORT diagram for details.

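### The rule excluding patients for non-attendance, and possibly for pain above 8 on the primary scale, is not reconciled with the stated intention-to-treat analysis

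*Protocol article*

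**What the plan says.** The exclusion rule stands in the Sequence generation section of the protocol article. Its subject is the patients in each group, who are to be removed under this wording: "excluded from the study if they have severe pain (above 8, according to NPRS-11) or did not attend three sessions". The sentence that follows it describes allocation: "After the initial evaluation, patients will be randomly assigned to one of the three study groups".

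The Statistical analysis section says: "The intention-to-treat protocol was followed for post-treatment analysis". It then refers the reader to the CONSORT diagram.

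The primary outcome is defined as "between- and within-group differences in the Numerical Pain Rating Scale (NPRS) at the second and third assessments", so the exclusion threshold and the primary outcome use the same scale.

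The eligibility section sets only a lower pain bound, "visual analog scale (VAS) greater than 3 from 10". Neither it nor the Exclusion criteria section contains an upper pain limit or an attendance rule.

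The NPRS section gives the category "severe pain (7–10"), whereas the exclusion rule attaches the word severe to scores above 8.

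**The concern.** An intention-to-treat analysis keeps every randomised patient in the allocated group, whatever happens afterwards. A rule that takes patients out of the study for what they do or score after allocation works against this, unless they are still followed and analysed. The text shown does not say that they are.

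The attendance part bears on the trial's main hypothesis, that pain neuroscience education with online exercise does better than the same education with face-to-face exercise. The Introduction calls consistency in home exercise a common problem, and the abstract expects online training to encourage patients to continue. Attendance may thus itself be an effect of the allocated delivery mode. If non-attenders are left out, the groups compared are attenders under two different regimes and no longer the groups formed by randomisation.

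The pain part, if it acts after allocation, would remove patients because of a high value on the primary outcome. More would go from the arm that is doing worse, which narrows a true difference and conceals worsening.

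**Working it through.** **Step 1: when each part of the rule can act.**

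- *Attendance.* The three education sessions over 2 weeks, and the exercise programme after them, belong to the group treatments and follow allocation (listing of groups, Interventions for experimental groups, Table 1). Attendance cannot be judged before randomisation. The wording does not say whether three sessions missed at any time are meant, or the three education sessions. On the first reading the rule could be strict: 3 days a week for up to 12 weeks is at most 3 × 12 = 36 exercise sessions, so a patient who attended 33 of them (33/36 = 92%) could be excluded. On either reading the rule acts after randomisation.
- *Pain above 8.* No time point is given. Three things favour a post-allocation rule: it refers to patients in each group, it shares a sentence with attendance, and the eligibility lists contain no upper limit. One thing points the other way: the sentence stands after the baseline data collection and before the randomisation sentence.

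**Step 2: size of the effect of the pain rule, if it acts after allocation and the excluded scores are not analysed.**

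Inputs from the Statistical analysis section: SD 2.5 and a difference of 2 points. The NPRS section gives an 11-point scale from 0 to 10. The article states no follow-up means, so these are assumed and varied. As orientation, if 2 points is 30%, the implied reference level is 2/0.30 = 6.7.

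Model: a normal score with mean μ and SD 2.5, rounded to whole numbers and limited to 0–10. The rule is applied at the assessment itself.

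- Proportion removed: P(score > 8) = 1 − Φ((8.5 − μ)/2.5).
- Mean after removal: Σ k·p(k) / Σ p(k), with both sums over k = 0 to 8.

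Example with means 6 and 4:

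- Removed in the worse arm: 1 − Φ(1.0) = 15.9%. Removed in the better arm: 1 − Φ(1.8) = 3.6%.
- Means with everyone kept: 5.95 and 4.05, difference 1.90. This is slightly below 2 because the scale is bounded.
- Means after removal: 5.28 and 3.85, difference 1.43.
- Shrinkage: 1 − 1.43/1.90 = 25%.

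| Assumed means, worse / better arm | Removed, worse arm | Removed, better arm | Difference, all kept | Difference after removal | Shrinkage |
|---|---|---|---|---|---|
| 4 / 2 | 3.6% | 0.5% | 1.75 | 1.59 | 9% |
| 5 / 3 | 8.1% | 1.4% | 1.86 | 1.56 | 16% |
| 6 / 4 | 15.9% | 3.6% | 1.90 | 1.43 | 25% |
| 6.7 / 4.7 | 23.6% | 6.4% | 1.88 | 1.29 | 31% |
| 7 / 5 | 27.4% | 8.1% | 1.86 | 1.23 | 34% |

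The rows with 6.7 and 7 suppose that the worse arm stays at or above the implied reference level, although every arm receives education and exercise.

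**Step 3: the attendance rule.** The article gives no expected attendance by group and no relation between attendance and pain. No size can be calculated, and the bias could go either way.

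**The case against.** A reader might infer that the article plans to drop randomised patients whose follow-up pain exceeds 8 and to delete their scores. The documents do not support that as a stated plan, for two reasons. The pain sentence precedes the randomisation sentence, so a cap on baseline pain is possible; on that reading the rule would not select on the outcome, and the calculation above would not apply. Also, being excluded from the study is not the same as having one's data deleted. No section says that such data are discarded, the CONSORT diagram to which the analysis section refers is not shown, and the handling of missing data is to be settled at a data review meeting before analysis. Both points stand, and they limit the pain part to a conditional claim.

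Two further readings go too far. The exclusion cut-off is not given two values: it appears once, as above 8. Only the word severe is used in two ways, and the NPRS section itself treats its categories as rough. Nor does the statement in the Randomization section, "Patients can discontinue the project at any time because of participant request or improving/worsening disease", add a conflict. Stopping at the patient's request or because the disease changes is compatible with intention to treat if follow-up and analysis continue.

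None of this answers the attendance part, which can act only after randomisation. Nor is it a matter of detail left out by a condensed article: the rule and the analysis principle are both stated, and the text shown does not fit them together.

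**Conclusion.** The point holds in this form. The attendance rule removes randomised patients from the study, and nothing shown reconciles it with the intention-to-treat statement. If those patients are not analysed, the online versus face-to-face comparison is biased by an unknown amount in an unknown direction. Confidence in this part is high.

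For the pain rule, confidence is lower because its timing is not stated. If it acts after allocation and the scores are left out, the observed difference shrinks by about 9% to 34%. That range rests on the article's SD and target difference, on assumed follow-up means, and on the rule being applied at the outcome assessment. If it is a baseline cap, there is no such shrinkage, and the defect is only that an entry criterion is missing from the eligibility lists.

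This should be settled before the analysis, because it decides whose outcomes are collected, and assessments not made cannot be recovered later.

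**What to change.** Reconcile the Sequence generation and Statistical analysis sections:

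- State that non-attendance, high pain or stopping treatment does not remove a randomised patient from the 2-week and 3-month assessments, nor from the primary analysis in the allocated group.
- Label any analysis restricted by attendance as secondary, and say which sessions the attendance rule counts.
- State when the pain limit applies. If it was meant as a baseline criterion, list it with the eligibility criteria and apply it before allocation.
- Reconcile the two uses of severe pain in the Sequence generation and NPRS sections.

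Simply deleting the sentence is not advised, since it may also serve as a clinical withdrawal rule. Whether and when a patient stops treatment is a separate clinical matter for the sponsor. The statistical requirement is only that stopping treatment be kept apart from follow-up and analysis.

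The cost is a change of wording and some added follow-up. The article allows the NPRS to be taken by phone, but the neck flexor endurance test is a physical examination and cannot be done that way. The primary analysis will also include some patients with poor adherence.

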**Fig. 1 Fig1:**
[figure not shown]
CONSORT diagram. PNE, pain neuroscience education

Groups will receive different treatment programs as follows:Group 1: PNE with an online exercise intervention once a day, 3 days a week, for up to 12 weeksGroup 2: PNE with a face-to-face exercise intervention once a day, 3 days a week for up to 12 weeksGroup 3: Neck biomechanical education with the recommendation to be active daily and perform a few common physiotherapy exercises once a day, 3 days a week, for up to 12 weeks

### Ethical aspects

Before starting the project, all patients will be asked to complete and signed an informed consent form. Ethics approval was obtained on 11/7/2021, from the Ethics Committee on Research at Kharazmi University, Iran (IR.KHU.REC.1400.013). Furthermore, the protocol was approved at the Iranian Registry of Clinical Trials on 2021-10-07 (IRCT20150503022068N5).

### Study participants and eligibility criteria

The patients with chronic non-traumatic neck pain who meet the following criteria will be accepted as participants in the trial: patients with chronic nonspecific and non-traumatic neck pain of at least 3 months, visual analog scale (VAS) greater than 3 from 10, both sexes range from 18 to 65, accept to take part in the research, and sign the information concept [27].

### Exclusion criteria

The patients will be excluded if they have previous history of neck or back surgery, neurological signs, rheumatoid arthritis in the past 3 years, taking part in any other therapies, and start new medication 6 weeks prior to and during participation in this trial [27].

Also, patients with chronic pain syndromes (e.g., fibromyalgia, chronic fatigue syndrome) will be excluded to obtain a homogeneous population [33].

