### Allocation concealment mechanism

After the initial evaluation, patients will be randomly assigned to one of three study groups (PNE as an experimental group) and pain biomechanics education (control group) by selecting numbers from 1 to 120, which will be pre-prepared and packaged in sealed envelopes by an independent person. The randomization sequence will not be disclosed until patients complete their baseline assessments. The statistician and the assessor will be blind to the group allocation. Patients will not be blind to the intervention, but do not know which group will be treatment therapy. The three groups in the study will be monitored by a physiotherapist and a corrective movement instructor.

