### Outcome variables

All variables will be assessed initially (before intervention), after PNE (after 2 weeks), and after exercise intervention (after 3 months). The flow chart can be seen in Fig. 1. After filling in the questionnaires by the patients, they will be asked about taking any painkillers and psychological medication. The completed questionnaires will be handed over to a skilled psychiatrist who will be blind to assigning patients to study groups. The psychiatrist will consider if it is necessary for any of the patients to take any psychological medication.

Personal information about potential and enrolled participants will be collected, shared, and maintained to protect confidentiality before, during, and after the trial.

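### As worded, the new-medication criterion makes a medication start after randomisation a ground for exclusion, which conflicts with the stated intention-to-treat analysis

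*Protocol article*

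**What the plan says.** The Exclusion criteria section lists, among conditions such as earlier surgery and neurological signs, patients who "start new medication 6 weeks prior to and during participation in this trial". The stated consequence is exclusion. No drug class is named, so a new painkiller counts.

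On timing, the Sequence generation section says "After the initial evaluation, patients will be randomly assigned to one of the three study groups", and the Allocation concealment mechanism section agrees: "The randomization sequence will not be disclosed until patients complete their baseline assessments". Two weeks of education and 12 weeks of exercise come after that.

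On analysis, the Statistical analysis section says "The intention-to-treat protocol was followed for post-treatment analysis". The Randomization section states the aim "However, all efforts will be made to avoid missing data" and leaves the handling of missing data to a data review meeting. The primary outcome is the "Numerical Pain Rating Scale (NPRS) at the second and third assessments", that is, after 2 weeks and after 3 months.

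Two other places bear on the reading. The Sequence generation section has a separate rule for patients already allocated, which begins "Patients in each group will be excluded from the study if they have severe pain" and also covers missed sessions. The Outcome variables section says of patients who have filled in the questionnaires that "they will be asked about taking any painkillers and psychological medication", and has a blinded psychiatrist consider whether any patient needs psychological medication.

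**The concern.** An eligibility criterion can be judged only on what is known at entry. A medication start during participation is not known then. If it is a ground for exclusion, it acts on randomised patients according to what happens to them after allocation, and an intention-to-treat analysis is meant to prevent exactly that.

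Starting a new drug in a neck-pain trial is unlikely to be unrelated to outcome: patients whose pain or distress is worse are the plausible starters. If they leave, the 3-month pain scores are lost selectively. An arm that loses more of its worst patients then looks better than it is. The direction depends on which arm that is. The 2-week assessment is less exposed because little time has passed.

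Rates could differ by arm. Patients are not blinded, and the online arm has round-the-clock support while the other patients are normally answered in person once a week. The documents do not show whether rates do differ.

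**Working it through.** **Step 1: set the text side by side.**

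- Exclusion criteria: a medication start during participation leads to exclusion.
- Sequence generation and Allocation concealment mechanism: baseline assessment first, then allocation. Almost all participation is therefore after randomisation.
- Statistical analysis: intention-to-treat.
- Nothing in the article limits the criterion to screening, and nothing says that patients who meet it later stay in follow-up or in the analysis.

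The conflict follows from the wording alone and needs no figure.

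**Step 2: size it.** The plan gives no rate of medication starts, so there is no figure of its own to reproduce.

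- From the Statistical analysis section: SD 2.5 NPRS points; design difference 2 points.
- Assumed: 10% removed in one arm and 5% in the other. With numbers 1 to 120 in the envelopes (40 per arm) that is 4 v 2 patients. With 88 per group it is about 9 v 4. The article implies both arm sizes, but the expected shift does not depend on arm size.
- Assumed: removed patients average d SDs above their arm's mean.

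If a share p with mean +d SD is removed, the mean of those left falls by p × d / (1 − p) SD. The spurious between-arm difference is the gap between the two falls, multiplied by 2.5.

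| d | Fall at 10% (SD) | Fall at 5% (SD) | Gap (SD) | NPRS points | Share of 2 points |
|---|---|---|---|---|---|
| 0.5 | 0.0556 | 0.0263 | 0.029 | 0.07 | 4% |
| 1.0 | 0.1111 | 0.0526 | 0.058 | 0.15 | 7% |
| 1.5 | 0.1667 | 0.0789 | 0.088 | 0.22 | 11% |

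The last row is strong selection: the very top 10% of a normal distribution averages 1.75 SD.

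**Step 3: selection on distress instead of pain.** If removed patients are 1.5 SD worse on distress, and distress correlates 0.3 to 0.5 with pain (assumed), the shift is 0.219 × 0.3 = 0.07 to 0.219 × 0.5 = 0.11 points.

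**Step 4: larger imbalances.** A simulation with no true effect, 96 per arm (288 / 3), and a latent correlation of 0.3 to 0.5 between pain and being removed gave, over 1,500 replicates per setting:

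| Removed | Spurious difference (points) | Type I error |
|---|---|---|
| 10% v 10% | about 0 | about 5% |
| 20% v 10% | 0.13 to 0.19 | about 6% to 8% |
| 30% v 10% | 0.20 to 0.38 | about 8% to 17% |

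None of these removal rates comes from the documents. If medication also lowers the scores of the patients who are kept, the gap between the two analyses is smaller still.

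**The case against.** The strongest reply is that this is an entry criterion. The Sequence generation section has the inclusion and exclusion criteria collected by online questionnaire and checked by a physician, before consent, baseline and allocation. In such a list, the words about participation could mean that no new medication is planned. The section's explicit rule for removing allocated patients names severe pain and missed sessions, not medication. A trial in which a psychiatrist considers whether patients need medication does not obviously intend to drop those who start it. Intention-to-treat is already declared, exclusion might mean stopping treatment only, and details of the analysis set often sit in a full protocol or SAP that is not shown.

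Part of this stands. The literal reading is not certain, and the point has to be confined to what the wording allows. But a planned start is not what the criterion describes, and the article nowhere states the milder meaning. Where it does speak of exclusion after allocation, it says from the study; that does not settle how the medication criterion is applied, but it gives no support to a softer sense of the word. The medication question could serve to enforce the criterion as easily as to record an event. The declaration of intention-to-treat is one side of the conflict, so it cannot also resolve it.

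It is also fair that the likely bias is modest. Every 10% v 5% result lies below the minimal detectable change of 0.45 that the article quotes for the NPRS. The severe-pain rule selects on the primary outcome directly and is the more serious problem of the two. Those facts limit the weight of this point without removing it.

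**Conclusion.** The concern holds as a statement about the wording. The criterion turns a post-randomisation event into a ground for exclusion, contradicts the stated intention-to-treat analysis and works against the aim of avoiding missing data. Whether anyone was removed under it cannot be told from the article.

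The size is unknown. Under an assumed 10% v 5% removal, 3-month NPRS would shift by 0.07 to 0.22 points. It would take larger, unsourced imbalances to approach 0.4 points, and balanced removal does essentially no harm. This is a modest risk to a primary time point that is cheap to close, so the wording should be changed. Confidence is medium, because an entry-only intention remains possible.

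**What to change.** Apply new medication as an exclusion criterion only to the 6 weeks before baseline. Add one sentence: patients may be asked to avoid new medication during the trial, but any randomised patient who starts it remains in follow-up and is analysed in the group to which they were randomised. Record the start through the medication question in the Outcome variables section.

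The Trial status section describes the trial as underway. For patients already enrolled, keep or restore them in the analysis set wherever outcomes exist or can still be collected.

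The cost is one reworded criterion and one added sentence, with no new data collection. Some outcomes will then include an effect of added medication, a normal consequence of the intention-to-treat analysis already chosen. Rewording cannot recover outcomes never collected from patients already removed.
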